## 2. Method and Analysis

### 2.1. Trial Design

This study is a phase 2, dose-finding, double-blind, randomized placebo-controlled trial to evaluate the efficacy and safety of two different doses of USL, compared with a placebo, for DED treatment. The trial will be conducted at Daejeon University Daejeon Korean Medicine Hospital and is set to start recruitment in January 2025. Participants who sign a written informed consent form after receiving a comprehensive explanation of the trial will be screened, and 120 participants will be enrolled after the eligibility assessment. Eligible subjects will be randomized into three groups in a 1:1:1 allocation ratio: standard-dose USL (1 g/day), high-dose USL (2 g/day), and placebo groups. The subjects would be asked to administer one of the medications twice a day for 12 weeks and visit five times (at screening, baseline, week 6, week 12, and week 14) to evaluate the efficacy and safety outcomes (Figure 1, Table 1). This study follows the guidelines of the Standard Protocol Items: Recommendations for Interventional Trials (SPIRIT) [30] and will be conducted in compliance with ethical principles in the Declaration of Helsinki and Good Clinical Practice guidelines [31].

This study protocol was approved by the Institutional Review Board of Daejeon University Daejeon Korean Medicine Hospital (DJDSKH-23-DR-11), and registered at Clinicaltrials.gov (NCT06016010).

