#### 2.6.4. Safety Outcomes

Adverse events (AEs), vital signs, laboratory examinations, visual acuity, and IOP will be assessed throughout the trial to evaluate safety. At every visit, AEs, vital signs, visual acuity, and IOP will be observed, and laboratory tests will be performed before and after taking the trial medication. We will record every unexpected symptom or sign during the trial by asking the participants questions and through the investigator’s examination. However, if serious AEs occur during the trial, the patient will be immediately removed from the trial and proper treatment will be provided. Visual acuity and IOP will be examined as recommended by the Ministry of Food and Drug Safety in Korea for clinical trials on ocular diseases. The laboratory tests will include liver function, routine blood, and urine tests.

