### 2.7. Statistical Analysis

Statistical analyses of all outcomes will be conducted by an independent statistician using SAS Version 9.4 Analytics Pro software. Continuous variables will be presented as the mean ± SD and categorical variables will be presented as frequencies and percentages. For efficacy analysis, a full analysis set (FAS) based on intention-to-treat (ITT) analysis will be performed as the primary analysis, and PP analysis will be used for secondary analysis. All randomized participants who are evaluated at least once after administration of the trial medication will be included in the FAS, and only those who complete the trial without violating the protocol will be included in the PP set. A safety analysis will be conducted for all participants who are randomized and administered the trial medication at least once.

The primary and secondary efficacy outcomes will be analyzed using the mixed-effects model for repeated measures, with each group and visit set as fixed effects and participants as random effects. In addition, the difference between pre- and post-treatment within groups will be analyzed using Student’s paired *t*-test or Wilcoxon signed-range test, depending on normality. A multiple imputation method will be used for missing values. The efficacy of USL will be accepted at a significance level of 2.5% in both TBUT and OSDI compared with the placebo, whereas other secondary outcomes will be accepted at a 5% significance level.

To analyze safety outcomes, Fisher’s exact test will be used to compare the number of AEs between the groups, and Student’s paired *t*-test or the Wilcoxon signed-rank test will be performed to analyze the differences between pre- and post-treatment laboratory variables, vital signs, visual acuity, and IOP. Demographic characteristics will be analyzed using the Wilcoxon rank-sum test or independent *t*-test for continuous variables and Fisher’s exact test or the chi-square test for categorical variables.

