## 3. Discussion

Despite the growing burden of DED on public health, current treatments for DED present unmet medical needs owing to their side effects or ineffectiveness. Clinicians and patients with DED seek better treatment therapies to manage inflammation and ocular symptoms; nutritional supplements or complementary medicine have emerged as promising candidates for DED by managing ocular surface inflammation [51]. As inflammation is recognized as a major factor in the pathogenesis of DED, we anticipate that the anti-inflammatory effects of USL would improve the symptoms and signs of DED.

Our trial was designed to evaluate the efficacy and safety of USL for DED compared with a placebo and to determine the appropriate dosage of USL. We plan to conduct a phase 2, double-blind, dose-finding, randomized placebo-controlled trial, and both objective signs and subjective symptoms of DED, as well as cytokines related to inflammation, will be investigated. Objective signs and subjective symptoms are important in the diagnosis and management of DED; however, previous studies have reported a lack of association between them, making DED more complicated. The Food and Drug Administration (FDA) recommends that the efficacy of treatment should be demonstrated by showing significant differences in objective prespecified signs and subjective prespecified symptoms of dry eye. Moreover, the FDA suggests that different endpoints for objective signs (conjunctival staining, corneal staining, Schirmer’s test score, and TBUT) or subjective symptoms should be conducted when designing clinical trials for the treatment of DED. According to the FDA guidelines, we will evaluate TBUT and OSDI as primary outcomes and other objective endpoints, including fluorescein corneal staining score, Schirmer’s test, meibomian gland test, and subjective endpoints of VAS and SPEED-II as secondary outcomes. In addition, to investigate the inflammatory effects of USL, cytokines IL-1β, IFN-γ, and TNF-α will be measured.

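### Safety compared with placebo is an aim, but for laboratory values, vital signs, visual acuity and IOP the plan names only a pre/post test, which makes no comparison with placebo

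*Protocol article*

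**What the plan says.** Section 2.1 gives the purpose of the trial as to "evaluate the efficacy and safety of two different doses of USL, compared with a placebo, for DED treatment". The Discussion repeats it: to "evaluate the efficacy and safety of USL for DED compared with a placebo and to determine the appropriate dosage of USL".

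Section 2.6.4 lists the safety data as adverse events, vital signs, laboratory tests, visual acuity and IOP. It adds: "At every visit, AEs, vital signs, visual acuity, and IOP will be observed". Table 1 agrees: vital signs, acuity and IOP are taken at all five visits, laboratory tests only at screening and week 12.

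Section 2.7 assigns the methods as follows.

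- **Primary and secondary efficacy outcomes:** a repeated-measures mixed model "with each group and visit set as fixed effects and participants as random effects". The paired test is an extra: "In addition, the difference between pre- and post-treatment within groups will be analyzed using" a paired t-test or its rank counterpart.
- **Adverse events:** Fisher's "exact test will be used to compare the number of AEs between the groups".
- **Laboratory values, vital signs, acuity and IOP:** a paired t-test or signed-rank test, which "will be performed to analyze the differences between pre- and post-treatment laboratory variables, vital signs, visual acuity, and IOP".
- **Demographic characteristics:** two-sample and contingency-table tests.

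The section also says in general terms that continuous variables are summarised by mean and SD and categorical variables by counts and percentages.

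**The concern.** The method named for these four kinds of safety data does not address the stated question. A paired test asks whether the mean changed over time in the participants analysed. Season, repeat measurement, regression to the mean after eligibility limits on IOP, blood pressure, liver enzymes and creatinine, or a placebo response can all move that mean. Any such movement common to the three arms counts as a change in each. The placebo arm exists to remove it, and the paired test does not use the placebo arm.

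The contrast within section 2.7 makes this a stated choice and not just brevity. For efficacy the paired test supplements a model with a group effect, and for adverse events the test is between groups. For these four it stands alone.

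What is at stake is the reading of the safety results. Separate pre/post p-values for each arm invite the inference that a change significant on one USL dose but not on placebo is an effect of that dose. That pattern is not evidence of a difference between arms.

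**Working it through.** **Arm size.** The article's own sample size gives the number per arm. Section 2.2.3 assumes a TBUT difference of 1.3, SD 1.8, power 0.8, two-sided 0.05 and 20% dropout. The normal formula gives 2 × (1.960 + 0.842)² × 1.8² / 1.3² = 30.1, so 31 per arm. The t-based solution is 31.09, so 32 per arm, and 32 / 0.8 = 40, or 120 in three arms. This reproduces the stated figure. The range used below is therefore n = 32 (after dropout) to n = 40 per arm.

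**Assumptions.** The document gives no SD or expected change for any safety variable. Let d be a mean change shared by all three arms, in units of the SD of change, with no USL effect. Changes are normal, and the paired test is run in each arm. The safety sentence does not say that it is run by arm; pooling the arms would say even less about USL.

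**Formulas.**

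- p = probability that the two-sided 5% paired t-test is significant in one arm, from the noncentral t with n − 1 degrees of freedom and noncentrality d√n.
- A = probability that at least one USL arm is significant and placebo is not = (1 − p) × [1 − (1 − p)²].
- B = probability that one USL dose is significant and the other is not = 2p(1 − p).

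Example, n = 32, d = 0.3: p = 0.376; A = 0.624 × (1 − 0.624²) = 0.381; B = 2 × 0.376 × 0.624 = 0.469.

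| d (SD) | n | p | A | B |
|---|---|---|---|---|
| 0 | 32 or 40 | 0.050 | 0.093 | 0.095 |
| 0.2 | 32 | 0.195 | 0.283 | 0.314 |
| 0.2 | 40 | 0.235 | 0.317 | 0.359 |
| 0.3 | 32 | 0.376 | 0.381 | 0.469 |
| 0.3 | 40 | 0.457 | 0.383 | 0.496 |
| 0.4 | 32 | 0.592 | 0.340 | 0.483 |
| 0.4 | 40 | 0.694 | 0.277 | 0.425 |
| 0.5 | 32 | 0.782 | 0.207 | 0.341 |
| 0.5 | 40 | 0.869 | 0.128 | 0.227 |

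A cannot exceed 0.385. At larger drifts it falls again, because every arm becomes significant.

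**Direct comparison.** A two-sample test of change removes a shared d exactly. Its error is 5% for each dose against placebo and about 9% for either dose, whatever the drift. In simulation the rates were 0.048 to 0.053 for one dose and 0.087 to 0.094 for either. The like-for-like contrast with A is therefore about 9% against 13% to 38%.

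**Precision of the fix.** For mean change in IOP, assume an SD of 2 to 3 mmHg. The half-width of the 95% CI for dose minus placebo is t × SD × √(2/n). This gives 1.99 × 2 × √(2/40) = 0.89 mmHg at best and 2.00 × 3 × √(2/32) = 1.50 mmHg at worst.

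**The case against.** The strongest reply is that this is a journal article. By-arm change tables and abnormality counts usually sit in the full protocol or SAP, and naming a paired test does not rule them out. The trial has a randomised placebo arm, and means and SDs by arm would show placebo beside each dose. Adverse events are compared between groups, and the investigators undertake that "We will record every unexpected symptom or sign during the trial", including what examination finds, so a marked rise in IOP or loss of acuity could surface there. The illustrated rates depend on assumed drift; with no drift the misleading pattern occurs in 9%, no more than with direct comparisons of two doses.

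Much of this stands, and it limits the size of the point. It does not remove it. The article is not silent: it names the test, and that test cannot make the comparison in the aim. Side-by-side means give no estimate of the difference with its uncertainty.

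Three stronger readings are tempting but unsupported.

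- **That comparing significance across arms is the only reading open to the investigators.** The by-arm summaries and the adverse-event test exist, and nothing says the paired p-values will be compared across arms.
- **That dose choice would go wrong.** Nothing ties dose choice to these variables; the only acceptance rule in section 2.7 concerns TBUT and OSDI.
- **That a USL effect would be hidden if IOP fell on placebo and stayed flat on USL.** With an assumed fall of 1.5 mmHg and SD of 2 to 3 mmHg, the placebo arm's own paired test would be significant in about 78% to 99.6% of trials, so the contrast would be visible.

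Nor is it a fair criticism that a paired test is poor at finding two or three marked rises; the text does not give it that task.

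**Conclusion.** The concern holds as a minor mismatch between aim and method. For laboratory values, vital signs, visual acuity and IOP, the only named test cannot separate a USL effect from a change shared by all arms. Under an assumed shared drift of 0.2 to 0.5 SD, no USL effect and 32 to 40 per arm, a USL-only signal would appear in about 13% to 38% of trials for a given variable, against 9% with no drift. These rates illustrate the mechanism and do not predict this trial, because the drift is unknown. That the paired test makes no comparison with placebo needs no assumption. The primary efficacy result, the sample size and the adverse-event comparison are unaffected. An SAP that is not shown may already add the missing comparison.

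**What to change.** Amend section 2.7, before unblinding, as follows.

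1. Keep the paired tests, labelled descriptive.
2. For each USL dose, report the difference from placebo in change from baseline with a 95% CI.
   - IOP, acuity and vital signs: use the repeated-measures model already named for efficacy, with the week-0 value as covariate. Weeks 6 and 12 are on treatment. Show week 14 separately as off-treatment, since dosing lasts 12 weeks.
   - Continuous laboratory values: compare arms at week 12, adjusted for the screening value. Table 1 has no other laboratory times.
3. Optionally, tabulate by arm in the safety set the number newly beyond prespecified limits: AST/ALT and creatinine at or above twice the upper limit of normal, systolic pressure of 160 mmHg or more or diastolic above 100 mmHg, and IOP above 22 mmHg in each eye. The IOP limit must be declared as a new reporting limit, because exclusion criterion 6 is worded for more than one side.

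The cost is a few sentences and a few more tables, with no new data, visits or staff. Intervals will be wide, about ±0.9 to ±1.5 mmHg for mean IOP under the SDs assumed above. Two doses across several variables without adjustment will produce some chance findings, so these comparisons should be declared descriptive. The gain is a safety display that refers to placebo, not a powered safety test.

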### 2.8. Data Collection, Management, and Monitoring

All clinical trial data will be recorded, processed, and preserved to enable accurate reporting, interpretation, and confirmation in accordance with the Good Clinical Practice guidelines. Investigators will be acquainted with the trial protocol and follow the standard operating procedures of this trial.

Data collected at each visit from the source documents of each participant will be entered into an electronic case report form and managed by a data manager during the trial period. All data will be coded to maintain confidentiality, and only the principal investigator will be able to access the data. Throughout the study, full-source data verification will be conducted by a clinical research associate and the data manager.

Data monitoring will be conducted via regular and occasional visits, based on the monitoring plan. At each monitoring stage, the clinical research associate will check whether the trial is being conducted in compliance with the protocol and related regulations. All data will be collected accurately, and AEs will be properly reported. Any problems encountered during the trial will be resolved by the investigators.

### 2.9. Ethics Approval and Dissemination

All subjects will be provided with all information related to this trial, including the entire trial process, possible benefits and risks of intervention, other therapeutic options for the target disease, and the right to withdraw from the trial. The potential unintended adverse events of intervention, including stomach discomfort, anorexia, nausea, and diarrhea, which are commonly observed in herbal medicines, will also be informed to each subject. After sufficient time and opportunity to ask questions about the trial, participants will be asked to sign a written consent form. Every participant will be immediately notified of any changes or factors that may affect them. After the trial has ended, the study results will be disseminated through peer-reviewed journals and a registry of clinical trials.

## 3. Discussion

Despite the growing burden of DED on public health, current treatments for DED present unmet medical needs owing to their side effects or ineffectiveness. Clinicians and patients with DED seek better treatment therapies to manage inflammation and ocular symptoms; nutritional supplements or complementary medicine have emerged as promising candidates for DED by managing ocular surface inflammation [51]. As inflammation is recognized as a major factor in the pathogenesis of DED, we anticipate that the anti-inflammatory effects of USL would improve the symptoms and signs of DED.

Our trial was designed to evaluate the efficacy and safety of USL for DED compared with a placebo and to determine the appropriate dosage of USL. We plan to conduct a phase 2, double-blind, dose-finding, randomized placebo-controlled trial, and both objective signs and subjective symptoms of DED, as well as cytokines related to inflammation, will be investigated. Objective signs and subjective symptoms are important in the diagnosis and management of DED; however, previous studies have reported a lack of association between them, making DED more complicated. The Food and Drug Administration (FDA) recommends that the efficacy of treatment should be demonstrated by showing significant differences in objective prespecified signs and subjective prespecified symptoms of dry eye. Moreover, the FDA suggests that different endpoints for objective signs (conjunctival staining, corneal staining, Schirmer’s test score, and TBUT) or subjective symptoms should be conducted when designing clinical trials for the treatment of DED. According to the FDA guidelines, we will evaluate TBUT and OSDI as primary outcomes and other objective endpoints, including fluorescein corneal staining score, Schirmer’s test, meibomian gland test, and subjective endpoints of VAS and SPEED-II as secondary outcomes. In addition, to investigate the inflammatory effects of USL, cytokines IL-1β, IFN-γ, and TNF-α will be measured.

This is the first clinical trial to evaluate the efficacy and safety of USL for DED. Along with our results, which will show the effects of USL in inducing tear secretion, improving corneal irregularity, and ameliorating inflammation on the ocular surface, we expect that USL will have effects on DED. USL is safe and has little risk of side effects, as it is already considered a Korean medicine or functional food in Korea. With this experimental and empirical evidence, our study results will provide new evidence for the efficacy and safety of USL on DED in a well-designed trial following the FDA guidelines.

This trial protocol has some limitations. First, as our trial is the first study to evaluate USL in DED, the sample size cannot be calculated based on the exact effect size of USL. Thus, we estimated the effect size based on the results of previous studies in which a similar effect was expected. Second, our trial will be conducted at a single hospital, which can create bias, as a recent epidemiological study of binary outcomes reported that single-center trials showed larger intervention effects than multicenter trials. Recruiting subjects only in Korea may also cause bias in the same context. Third, our exclusion criteria can reduce external validity, though severe restrictions are needed to achieve approval from the Ministry of Food and Drug Safety for clinical trials. Finally, as our trial has a 14-week trial period, maintaining the compliance of the patient is an important issue, and strategies to prevent dropout will be needed. However, we will compensate for this risk by carefully evaluating the methodology and enrolling a sufficient number of participants to demonstrate treatment differences. Further multicenter studies with an accurately calculated number of samples will be conducted to confirm the efficacy and safety of USL.

## Figures and Tables

**Figure 1 healthcare-12-02383-f001:**
[figure not shown]
Flowchart of the trial process.

**Table 1 healthcare-12-02383-t001:** Schedule of enrolment, interventions, and assessments.

	Study Period				
	Enrolment	Allocation	Post-Allocation		Follow-Up
Visit	1	2	3	4	6
Timepoint	−2 week	0	6 weeks ± 7 days	12 weeks ± 7 days	14 weeks ± 7 days
Enrolment:					
Eligibility screen	X				
Informed consent	X				
Demographics	X				
Medical and treatment history	X				
Physical examination	X				
Vital sign	X	X	X	X	X
Visual acuity, IOP	X	X	X	X	X
Laboratory tests	X			X	
EKG	X				
Allocation		X			
Interventions:					
Standard-dose USL					
High-dose USL					
Placebo					
Assessments:					
OSDI	X		X	X	X
TBUT	X		X	X	X
VAS		X	X	X	X
Schirmer’s test		X	X	X	X
Meibomian gland test		X	X	X	X
FCS	X		X	X	X
SPEED-II		X	X	X	X
Biomarkers		X		X	
Adverse events		X	X	X	X
Compliance test			X	X	

“X” indicates procedures occurring at the designated time points. EKG: Elektrokardiogram; IOP: intraocular pressure; OSDI: Ocular Surface Disease Index; TBUT: tear break-up time; VAS: visual analog scale; FCS: fluorescein corneal staining; SPEED-II: Standard Patient Evaluation for Eye Dryness-II; USL: Useul.

## Data Availability

The datasets used or analyzed during the current study will be available from the corresponding author upon reasonable request.
